### 6.3.2 Exclusion Criteria

1. For female subjects: pregnancy or lactating.
2. Subjects with chronic inflammatory articular disease other than SpA or systemic autoimmune diseases, e.g. systemic lupus erythematosus, Sjögren's syndrome, rheumatoid arthritis. *Other manifestations of SpA such as psoriasis, uveitis, peripheral arthritis are not regarded as exclusion criteria.*
3. History of inadequate response (primary non-response) to previous anti-TNF therapy. Patients who discontinued previous anti-TNF therapy or other biologics for reasons other than primary non-response may participate in the study if anti-TNF therapy is considered to be suitable in the opinion of investigator. This prior therapy must have been terminated at least 3 months (in case of TNF blockers or secukinumab) or 5 half-lives in the case of other biologics prior to Baseline visit.
4. Treatment with any other investigational drug within 3 months or 5 half-lives of the drug (whichever is longer) prior to Baseline visit.
5. History of intolerability or hypersensitivity reaction to Golimumab.
6. History of intolerability or hypersensitivity reaction to Celecoxib or Sulphonamides.
7. Previous reactions of asthma, urticaria or other severe hypersensitivity/reactions after intake of acetylsalicylic acid or other NSAIDs.
8. Known hypersensitivity to any component of the study medications.
9. Treatments with DMARDs other than methotrexate or sulfasalazine within 4 weeks prior to baseline (in case of leflunomide either 8 weeks or 4 weeks with a standard cholestyramine wash-out).
10. The presence of total spinal ankylosis.
11. Treatment with intravenous, intramuscular or intraarticular/periarticular steroids within 4 weeks prior to Baseline Visit, treatment with oral steroids in a dose of  $>10$  mg

- (prednisolone equivalent) per day.
12. Any active current infection. History of recurrent clinically significant infection (suggestive for primary or secondary immunodeficiency). Infections requiring treatment with antibiotics within 4 weeks prior to baseline.
  13. Current clinical signs and symptoms suggestive for tuberculosis.
  14. Positive tuberculosis IGRA serum test and abnormal chest x-ray (both at screening, maybe accepted if performed within 3 months prior to screening) suggestive for past or present tuberculosis (positive x-ray). *Patients with a positive Tuberculosis IGRA serum test but negative chest x-ray and without clinical symptoms suggestive for tuberculosis may participate in the study after initiation of standard prophylactic anti-tuberculous treatment, which has to be started 4 weeks before initiation of study medication and has to be taken for a total of 9 months.*
  15. Chronic infection with hepatitis B virus (*in case of HBsAg negativity, but anti-HBc positivity, participation in the study possible after hepatologists consultation*):. (see also table in section 6.7).
  16. Actual malignancies or history of malignancies with curative treatment within 5 years prior to screening, except successfully treated non-metastatic squamous-cell or basal-cell carcinoma of the cutis or carcinoma in situ of the cervix.
  17. History of demyelinating disease (like multiple sclerosis; including myelitis) or neurologic symptoms suggestive of demyelinating disease.
  18. History of cardiovascular events: myocardial infarction, stroke or transient ischemic attack, pulmonary embolism.
  19. Diagnosis of the coronary heart disease or peripheral arterial occlusive disease; uncontrolled arterial hypertension.
  20. High cardiovascular risk as assessed by the presence of >2 cardiovascular risk factors (e.g., uncontrolled hypercholesterolemia, diabetes mellitus, smoking, uncontrolled arterial hypertension).
  21. History of oesophageal, gastric, pyloric channel or duodenal ulceration documented by endoscopy/radiographic examination at any time before the screening visit, or any clinically relevant gastrointestinal bleeding, perforation, or gastric outlet obstruction.
  22. History of a chronic inflammatory bowel disease (Crohn's disease or ulcerative colitis).
  23. Evidence of other severe uncontrolled gastrointestinal, hepatic (serum albumin <25 mg/l or Child-Pugh-Score >10), renal, pulmonary, cardiovascular, nervous or endocrine disorders.

24. Increased bleeding risk including therapy with anticoagulants and thrombocyte aggregation inhibitors (e.g. low-dose aspirin).
25. Chronic or acute congestive heart failure (NYHA II to IV).
26. Patients with a history of a severe psychiatric illness, which might interfere with the patient's ability to understand the requirements of the study and assessment.
27. Diagnosis of fibromyalgia.
28. Alcohol abuse or illegal drug consumption in the last 12 months.
29. Vaccination with a live vaccine within 12 weeks prior to baseline.
30. Any of the following laboratory abnormalities as detected at screening:
  - Haemoglobin < 8.5 g/dl
  - Neutrophil counts < 2.000 /  $\mu$ l
  - Platelet count < 125.000 /  $\mu$ l
  - Aspartate aminotransferase (AST) or alanine aminotransferase (ALT) or alkaline phosphatase (AP) or gamma-glutamyl-transpeptidase (GGT) >3 times upper limit of normal
  - Creatinine > 1.4 mg / dl (= 120  $\mu$ mol / l).
31. Patients who are defined as "vulnerable patients": patients who are institutionalised due to regulatory or juridical order; patients who are an employee of the investigator or study site, with direct involvement in the proposed study or other studies under the direction of that investigator or study site; family members of the employees or the investigator.
32. Any other conditions making the patient unsuitable in the opinion of the investigator for the participation in the current study.
33. For patients participating in the MRI sub-study only: patients with contraindications for the magnetic resonance imaging (MRI) including but not limited to: claustrophobia, seizure disorders, presence of a implanted electronic devices (e.g., heart pacemaker, insulin pump, etc.), metal implants and metal foreign bodies in the patient's body suspected to be ferromagnetic, tattoos performed with metal-containing paints or tattoos of the large skin areas.

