|  | 
diseases, e.g. systemic lupus erythematosus, Sjögren's syndrome, rheumatoid arthritis. Other manifestations of SpA such as psoriasis, uveitis and peripheral arthritis are not regarded as exclusion criteria.
 
 
3. History of inadequate response (primary non-response) to previous anti-TNF therapy. Patients who discontinued previous anti-TNF therapy or other biologics for reasons other than primary non-response may participate in the study if anti-TNF therapy is considered to be suitable in the opinion of the investigator. This prior therapy must have been terminated at least 3 months (in case of TNF blockers or secukinumab) or 5 half-lives in the case of other biologics prior to Baseline visit.
 
4. Treatment with any other investigational drug within 3 months of 5 half-lives of the drug (whichever is longer) prior to Baseline visit.
 
5. History of intolerability or hypersensitivity reaction to Golimumab.
 
6. History of intolerability or hypersensitivity reaction to Celecoxib or sulphonamides.
 
7. Previous reactions of asthma, urticaria or other severe hypersensitivity/reactions after intake of acetylsalicylic acid or other NSAIDs.
 
8. Known hypersensitivity to any component of the study medications.
 
9. Treatments with DMARDs other than methotrexate or sulfasalazine within 4 weeks prior to baseline (in case of leflunomide either 8 weeks or 4 weeks with a standard cholestyramine wash-out).
 
10. The presence of total spinal ankylosis.
 
11. Treatment with intravenous, intramuscular or intraarticular/periarticular steroids within 4 weeks prior to Baseline Visit; treatment with oral steroids in a dose of >10 mg (prednisolone equivalent) per day.
 
12. Any active current infection. History of recurrent clinically significant infection (suggestive for primary or secondary immunodeficiency). Infections requiring treatment with antibiotics within 4 weeks prior to baseline.
 
13. Current clinical signs and symptoms suggestive for tuberculosis.
 
14. Positive tuberculosis serum IGRA test and/or abnormal chest x-ray (both performed at screening or within 3 months prior to screening) suggestive for past or present tuberculosis (positive x-ray). Patients with a positive tuberculosis serum test but negative chest x-ray and without clinical symptoms suggestive for tuberculosis may participate in the study after initiation of standard prophylactic anti-tuberculous treatment according to local guidelines.
 
15. Chronic infection with hepatitis B.
 
16. Actual malignancies or history of malignancies with curative treatment within 5 years prior to
 
 |

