### *Inclusion/Exclusion criteria*

Subjects should meet all inclusion and none of the exclusion criteria at both screening and Baseline Visits in order to be eligible for the study.

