| Negative     | Positive            | Referral to hepatologist:
Testing for HB virus load (PCR):
-negative – study participation possible, “watchful waiting”
-positive – anti TNF therapy might be discussed after initiation of pre-emptive HBV therapy |

Analyses for research purposes (blood tests for biomarkers of inflammation, bone / cartilage turnover, stool microbiome) will be performed centrally at the Charité Berlin and corresponding laboratories.

*Tuberculosis screening*

All patients will undergo an IGRA tuberculosis serum test (QuantiFERON®-TB Gold In-Tube test or T.SPOT TB®) and a chest x-ray (tests performed within three months prior to screening can be accepted) at Screening Visit. The history of active or latent tuberculosis infection as well as physical examination will be collected in order to reveal signs and

symptoms suggestive for tuberculosis. Patients with clinical or radiological signs suggestive for tuberculosis will be excluded from the study participation. Subjects with a negative tuberculosis serum test are eligible to continue with the screening procedures.

In case of a positive tuberculosis serum test but no radiological or clinical signs suggestive for tuberculosis the subject might participate in the study upon initiation of the prophylactic anti-tuberculous treatment (e.g., isoniazid 300 mg daily initiated 4 weeks prior to the first administration of Golimumab and continued for a total of 9 months in combination with pyridoxine).

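### Exclusion criterion 14 in Section 6.3.2 lets through an IGRA-negative patient whose chest x-ray suggests tuberculosis, whom the synopsis and Section 6.7 exclude

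*Protocol*

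**What the plan says.** The protocol states the tuberculosis rule in three places.

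- **Section 6.3.2, criterion 14:** "Positive tuberculosis IGRA serum test and abnormal chest x-ray", with the x-ray qualified as pointing to past or present tuberculosis. An exception lets IGRA-positive patients with a clear x-ray and no symptoms take part on prophylaxis, started 4 weeks before study medication and taken for 9 months.
- **Synopsis (Section 2), criterion 14:** "Positive tuberculosis serum IGRA test and/or abnormal chest x-ray", with the same x-ray qualifier and the same type of exception: "Patients with a positive tuberculosis serum test but negative chest x-ray and without clinical symptoms suggestive for tuberculosis may participate in the study" once prophylaxis has been started.
- **Section 6.7, Tuberculosis screening:** "Patients with clinical or radiological signs suggestive for tuberculosis will be excluded from the study participation". This sentence sets no IGRA condition. The next one adds: "Subjects with a negative tuberculosis serum test are eligible to continue with the screening procedures".

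Two other statements bear on the point. Section 6.7 requires both tests in everyone ("All patients will undergo an IGRA tuberculosis serum test", and a chest x-ray). It also ties eligibility to the criteria lists: "Subjects should meet all inclusion and none of the exclusion criteria at both screening and Baseline Visits".

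**The concern.** The two versions of criterion 14 differ in a logical connector, which changes who is excluded. With 'and', the chest x-ray has no effect when the IGRA is negative, although the protocol orders it for every patient. A site that checks the formal list in Section 6.3.2 literally could enrol a symptom-free patient with x-ray signs of past or present tuberculosis, against the synopsis and Section 6.7.

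The literal rule also runs the wrong way. An IGRA-positive patient with a clear x-ray must take prophylaxis, while an IGRA-negative patient with a suspicious x-ray passes criterion 14 with no prophylaxis at all.

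Patient safety is at stake. All Phase I patients receive golimumab, Section 9.2 names infections among its major potential risks, and Section 6.6.1 requires withdrawal if active tuberculosis is diagnosed. The conflict also leaves sites and monitors unable to say whether such an enrolment is a protocol deviation.

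**Working it through.** The protocol states no figure to reproduce. The check applies each of the three rules to a patient without clinical signs of tuberculosis, for every combination of IGRA result and chest x-ray (positive meaning suggestive of past or present tuberculosis).

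| IGRA | Chest x-ray | 6.3.2, criterion 14 | Synopsis, criterion 14 | 6.7, Tuberculosis screening |
|---|---|---|---|---|
| + | + | excluded | excluded | excluded |
| + | − | may enter on prophylaxis | may enter on prophylaxis | may enter on prophylaxis |
| − | + | **not excluded** | excluded | excluded |
| − | − | not excluded | not excluded | not excluded |

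The rules differ in 1 of 4 combinations.

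**Do other provisions close the gap?**

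- Criterion 13 ("Current clinical signs and symptoms suggestive for tuberculosis") concerns clinical findings, so an x-ray finding alone does not trigger it.
- Criterion 12 covers active current infection, but not x-ray evidence of past tuberculosis.
- Criterion 32 (unsuitable in the investigator's opinion) and inclusion criterion 6 (candidate for anti-TNF therapy in the investigator's opinion) are matters of judgement.
- The Section 6.7 sentence on IGRA-negative subjects lets them continue screening. It does not cancel the x-ray exclusion just before it, though a site working from Section 6.3.2 might read it that way.

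**Possible frequency.** The protocol gives no share p of IGRA-negative, x-ray-positive patients. As an assumption, take p from 0.1% to 2% of the 190 patients to be assessed for eligibility (synopsis). The expected number is 190p, and the chance of at least one is 1 − (1 − p)^190.

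| Assumed p | Expected number, 190p | Chance of at least one |
|---|---|---|
| 0.1% | 0.19 | 1 − 0.999^190 = 0.173 |
| 0.5% | 0.95 | 1 − 0.995^190 = 0.614 |
| 2% | 3.8 | 1 − 0.98^190 = 0.978 |

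These figures count patients who present at screening, not patients wrongly enrolled.

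**After correction.** With 'and/or' in Section 6.3.2 and the exception kept, the IGRA-negative, x-ray-positive patient is excluded in all three places and all four rows agree.

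**The case against.** The best defence is that the protocol as a whole already excludes this patient. Section 6.7 is the dedicated tuberculosis procedure, its exclusion sentence is mandatory, and the synopsis agrees with it. A wrongful enrolment needs a site to see the x-ray signs, disregard both texts and rely on one word in Section 6.3.2. Criteria 12 and 32 and inclusion criterion 6 narrow the remaining case further. The exception inside criterion 14 also suggests that either result was meant to count: under a literal 'and', an IGRA-positive patient with a clear x-ray would not be excluded and would need no permission. On this view it is a drafting slip of low importance.

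Much of this stands. The slip is more plausible than a deliberate second rule, and such a patient could be enrolled, not certainly would be. Meeting none of the exclusion criteria is a necessary condition for entry, not a sufficient one. The assumed frequency range has no basis in the protocol, and its results span most of the scale, so little weight should rest on it.

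None of this repairs Section 6.3.2. It is the formal exclusion list to which Section 6.7 refers, and its wording of this safety criterion is weaker than the rule evidently intended. The other provisions either do not reach x-ray evidence of past tuberculosis or depend on the investigator's judgement.

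**Conclusion.** The concern holds. As written, criterion 14 in Section 6.3.2 fails to exclude a symptom-free, IGRA-negative patient with a chest x-ray suggestive of past or present tuberculosis, and it conflicts with the synopsis and Section 6.7 on exactly that patient. This rests on the wording alone and needs no numerical assumption.

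The size is 1 of 4 test combinations, with an unknown and probably small number of patients. Only the illustrative counts depend on the assumed share of 0.1% to 2%.

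The consequence is for patient safety before anti-TNF exposure. Sample size, alpha and the randomised primary comparison are not affected, because this eligibility rule is applied before randomisation at week 12. The correction should be made, but the validity of the trial does not depend on it.

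**What to change.** In Section 6.3.2, criterion 14, replace 'and' with 'and/or' between the IGRA and chest x-ray conditions. Alternatively, state that a chest x-ray suggestive of past or present tuberculosis excludes the patient regardless of the IGRA result. Keep the exception for IGRA-positive, x-ray-negative, symptom-free patients on prophylaxis.

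As optional housekeeping in the same amendment, carry the 4-week lead time and 9-month duration of prophylaxis from Section 6.3.2 into the synopsis, which refers only to local guidelines.

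The cost is one connector or one sentence. Both tests are already required for all patients, so no procedure is added.

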|  | 
screening, except successfully treated non-metastatic squamous-cell or basal-cell carcinoma of the cutis or carcinoma in situ of the cervix.
 
 
17. History of demyelinating disease (like multiple sclerosis; including myelitis) or neurologic symptoms suggestive of demyelinating disease.
 
18. History of cardiovascular events: myocardial infarction, stroke or transient ischemic attack, pulmonary embolism.
 
19. Diagnosis of the coronary heart disease or peripheral arterial occlusive disease; uncontrolled arterial hypertension.
 
20. High cardiovascular risk as assessed by the presence of >2 cardiovascular risk factors (e.g., uncontrolled hypercholesterolemia, diabetes mellitus, smoking, uncontrolled arterial hypertension).
 
21. History of oesophageal, gastric, pyloric channel or duodenal ulceration documented by endoscopy/radiographic examination at any time before the screening visit, or any clinically relevant gastrointestinal bleeding, perforation, or gastric outlet obstruction.
 
22. History of a chronic inflammatory bowel disease (Crohn's disease or ulcerative colitis).
 
23. Evidence of other severe uncontrolled gastrointestinal, hepatic (serum albumin <25 g/l or Child-Pugh-Score >10), renal, pulmonary, cardiovascular, nervous or endocrine disorders.
 
24. Increased bleeding risk including therapy with anticoagulants and thrombocyte aggregation inhibitors (e.g. low-dose aspirin).
 
25. Chronic or acute congestive heart failure (NYHA II to IV).
 
26. Patients with a history of a severe psychiatric illness, which might interfere with the patient's ability to understand the requirements of the study and assessment.
 
27. Diagnosis of fibromyalgia.
 
28. Alcohol abuse or illegal drug consumption in the last 12 months.
 
29. Vaccination with a live vaccine within 12 weeks prior to baseline.
 
30. Any of the following laboratory abnormalities as detected at screening: 
 
Haemoglobin < 8.5 g/dl
 
Neutrophil counts < 2.000 / <math>\mu</math>l
 
Platelet count < 125.000 / <math>\mu</math>l
 
Aspartate aminotransferase (AST) or alanine aminotransferase (ALT) or alkaline phosphatase (AP) or gamma-glutamyl-transpeptidase (GGT) >3 times upper limit of normal
 
Creatinine > 1.4 mg/dl (= 120 <math>\mu</math>mol/l)
 
 
 
31. Patients who are defined as vulnerable patients according to Art. 10 REGULATION (EU) No 536/2014: patients who are institutionalised due to regulatory or juridical order; patients who are an
 
 |

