| Blood analysis i               | X j                       | X                    | X                       | X                       | X                       | X                        | X                         | X                         | X                         | X                         | X                         | X                         | X                         | X                                          |                                             |
| Biomarker blood samples k      |                                      | X                    |                         |                         |                         | X                        |                           |                           |                           | X                         |                           |                           |                           | X                                          |                                             |
| Urinalysis                                | X                                    | X                    |                         | X                       |                         | X                        |                           | X                         |                           | X                         |                           | X                         |                           | X                                          |                                             |
| Serum pregnancy test l         | X                                    |                      |                         |                         |                         |                          |                           |                           |                           |                           |                           |                           |                           |                                            |                                             |
| Stool samples m                |                                      | X                    |                         |                         |                         | X                        |                           |                           |                           |                           |                           |                           |                           | X                                          |                                             |

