g. BASDAI, ASDAS, PASS, PhASS, patient and physician global assessment only.

h. 12-lead electrocardiography (ECG).

i. Lab tests to be performed locally at the clinical trial site: Blood chemistry (total bilirubin, ALT, AST, GGT, AP, creatinine), hematology (erythrocytes, hemoglobin, leucocytes, neutrophils, lymphocytes, monocytes, basophils, eosinophils, platelets), CRP and ESR.

j. Lab test at screening should include also Quick-Test, International Normalized Ratio (INR) and activated Partial Thromboplastin Time (aPTT)

k. Biomarker blood samples (soluble and cellular markers of inflammation, cartilage and bone turnover) to be transferred to the Charité Universitätsmedizin Berlin.

l. Female patients of child-bearing potential only.

m. Stool samples for the microbiome analysis to be transferred to the Charité Universitätsmedizin Berlin.

n. Chest x-ray & tuberculosis serum IGRA test (QuantiFERON® TB Test or T SPOT.TB®) performed within 3 months prior to screening can be accepted.

o. X-rays of the lumbar and cervical spine, lateral views; to be performed at screening only if there is no image performed within 24 months prior to screening; at visit "Week 108/ET" – to be performed only at or after week 84 in case of early termination. All images of the spine to be transferred to the study coordinating centre at the Charité for central reading.p. For centres and patients participating in the MRI sub-study only. At visit "Week 108/ET" only to be performed at or after week 84 in case of early termination.

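### Exclusion 23 sets the serum albumin limit in mg/l in section 6.3.2 but in g/l in the synopsis, so the 6.3.2 limit is 1000 times too low

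*Protocol*

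**What the plan says.** Exclusion 23 keeps out patients with severe uncontrolled disease of several organ systems, and for the liver it gives two numerical markers in brackets. Protocol section 6.3.2 has: "serum albumin <25 mg/l or Child-Pugh-Score >10". The synopsis (section 2, exclusion criteria) carries the same criterion under the same number, with the albumin limit as "25 g/l or Child-Pugh-Score". The Child-Pugh limit is the same in both places; only the albumin unit differs.

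Section 6.7 (Inclusion/Exclusion criteria) requires that no exclusion criterion be met at either the screening or the baseline visit, so the printed limits are binding on sites.

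**The concern.** A numerical eligibility limit should read the same wherever the protocol prints it. Here the two current texts disagree by three orders of magnitude, and the wrong value is in the full criteria section. Read on its own, the albumin limb in 6.3.2 does no work, because no patient will have so low a value.

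Two people checking the same record against the two texts could therefore reach opposite answers on that limb. A patient with an albumin of 20 g/l meets it under the synopsis and does not under 6.3.2. What is at stake is a safety exclusion and the clean recording of protocol deviations. The treatment comparison is not affected.

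**Working it through.** **Inputs**
- Limit in section 6.3.2, criterion 23: 25 mg/l.
- Limit in the synopsis, criterion 23: 25 g/l.
- Range of patient albumin: not given in the protocol. Assumed here to be 5 to 50 g/l.

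**Conversion.** 1 g/l = 1000 mg/l.
- 6.3.2 limit in g/l: 25 / 1000 = 0.025 g/l.
- Ratio of the two limits: 25 / 0.025 = 1000.

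**Result of each limb for chosen values.** The rule is to exclude if albumin is below the limit.

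| Albumin (g/l) | 6.3.2 limb (<0.025 g/l) | Synopsis limb (<25 g/l) |
|---|---|---|
| 5 | not excluded | excluded |
| 20 | not excluded | excluded |
| 25 | not excluded | not excluded |
| 50 | not excluded | not excluded |

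The limbs disagree for every value from 5 to just under 25 g/l and agree from 25 g/l upwards.

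**Dependence on the assumed range.** The 6.3.2 limb excludes nobody as long as the lowest albumin is at least 0.025 g/l. The assumed floor of 5 g/l is 5 / 0.025 = 200 times that value, so the result does not hang on the exact floor chosen.

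**Which text is wrong.** The documents prove only that the units conflict. The direction is an inference: a limit that no patient can fall below cannot serve as a marker of severe liver disease, whereas 25 g/l lies inside the assumed range and separates patients. The error is therefore placed in 6.3.2.

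**What still applies if 6.3.2 is read literally.** The general wording on severe uncontrolled hepatic disease and the Child-Pugh limit in the same criterion remain. So do exclusion 15 (chronic hepatitis B), exclusion 30 (AST, ALT, AP or GGT above three times the upper limit of normal) and exclusion 32 ("Any other conditions making the patient unsuitable in the opinion of the investigator").

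**The case against.** The strongest reply is that this is an obvious slip with almost no consequence. A physician would be unlikely to apply a limit of 0.025 g/l, and the synopsis prints a workable one. The albumin figure is only a bracketed marker within a wider criterion. A patient with an albumin of 20 g/l from liver disease could still be excluded under the general wording, the Child-Pugh score or investigator judgement, so the criterion as a whole need not give a different decision for any patient. This stands, and it is why the disagreement is claimed for the albumin limb only.

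A second reply is that albumin is not in the scheduled chemistry, which lists "Blood chemistry (total bilirubin, ALT, AST, GGT, AP, creatinine", nor among the screening-only additions in footnote j of the assessment schedule. Correcting the unit therefore changes a limit against which no scheduled value is compared. This also lowers the practical effect. It is not itself an error: exclusion 23 asks for evidence of disease, unlike exclusion 30, which is tied to "Any of the following laboratory abnormalities as detected at screening". A value from the medical record can still be held against the limit, so the limit should be right.

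A third reply is that the protocol does not rank the synopsis above 6.3.2, and that the synopsis has a unit slip of its own: the estradiol limit is 30 nl/l there and 30 pg/ml in section 6.3.1. That shows the two lists were not reconciled for units. It does not make 25 mg/l a usable albumin limit.

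**Conclusion.** The point holds as a minor inconsistency. Section 6.3.2 states the albumin limit of exclusion 23 wrongly, by a factor of 1000 against the synopsis, and the albumin limb there cannot exclude anyone. The conflict and the factor are exact. That g/l is the intended unit rests on plausibility, with patient albumin assumed to lie between 5 and 50 g/l.

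The documents do not allow a count of patients who would be caught by the albumin limb alone; it is probably close to zero. The primary endpoint, its analysis and the sample size are untouched.

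**What to change.** In exclusion 23 of section 6.3.2, replace mg/l with g/l for serum albumin, so that it matches the synopsis. This is a one-unit correction with no effect on procedures, visits or cost, and it can be carried in the next protocol amendment.
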